### Hypotheses

This study has been designed to investigate four specific hypotheses relating to the effect of maternal and infant infections with geohelminths on host immune responses and development of allergic inflammatory diseases: 1) chronic exposures to geohelminth infections (i.e. maternal geohelminth infections and infant geohelminth infections within the first 2 years of life) suppress immune responses to childhood vaccines; 2) chronic exposures to geohelminth infections suppress aeroallergen skin test reactivity; 3) chronic exposures to geohelminth infections protects against the development of eczema; and 4) chronic exposures to geohelminth infections protect against the development of asthma but non-chronic exposures (i.e. later childhood exposures occurring after 2 years in the absence of maternal geohelminth infections) increase the risk of asthma.

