### Study power

The study sample size is fixed at 2,403 newborns. Primary outcome variables will be treated as statistically independent. Power calculations for primary study questions are shown in Table 2[58,59]. We expect a high degree of power for the estimation of most primary and secondary study outcomes (≥ 80% depending on immunological mechanism at α = 0.01) that will allow for the loss of power expected by controlling for confounding.

**Table 2 T2:** Power for analysis of primary exposure-outcome associations

Primary exposures (geohelminth infections)	Outcome	Sample size available	Analysis sample size	Exposure prevalence	Expected prevalence of outcomes (exposed vs. unexposed groups)	Α	Power
Maternal	Vaccine antibodies @ 7 mths						
	Hib	2,300	1,000	50%	65% vs. 75%	0.01	80%
	Rotavirus	2,300	1,000	50%	40% vs. 60%	0.01	> 99%
Maternal	Vaccine antibodies @ 2 yrs						
	TT	1,955	1,000	50%	85% vs. 95%	0.01	> 99%
	HBV	1,955	1,750	50%	80% vs. 85%	0.05	80%
	OPV type 3	1,955	500	50%	80% vs. 95%	0.01	> 99%
Infant	Vaccine antibodies @ 5 yrs						
	TT	1,725	1,000	35%	60% vs. 80%	0.01	99%
	HBV	1,725	1,500	35%	70% vs. 80%	0.01	95%
	OPV type 3	1,725	1,000	35%	50% vs. 70%	0.01	> 99%

Maternal	SPT @ 3 years	1,840	1,840	50%	15% vs. 25%	0.01	99%
Infant	SPT @ 3 years	1,840	1,840	35%	15% vs. 25%	0.01	> 99%

Maternal	Eczema @ 3 years	1,840	1,840	50%	25% vs. 35%	0.01	99%

Maternal	Asthma @ 5 years	1,725	1,725	50%	17% vs. 23% #	0.05	86%
Infant	Asthma @ 5 years	1,725	1,725	35%	17% vs. 23% #	0.05	83%
Infant	Asthma @ 5 years	1,725	1,207	20%	25% vs. 15% #	0.01	93%

Random samples of the study population will be selected for analysis of the protective levels of vaccine antibodies. Based on data from the cohort we estimate that 20% of children will have allergen skin test reactivity to any allergen at 5 years, that 30% of children will have at least one documented episode of eczema by 3 years of age and that 20% of children will have asthma at 5 years. Based on data from the cohort we estimate that ~50% of mothers are infected with any geohelminth parasite and ~30% of children will have at least one documented geohelminth infection during the first 2 years of life.

#-expected effects of geohelminth infections on asthma prevalence using data from cross-sectional analyses in Ecuador [58] and Brazil [59].

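### Table 2's two infant asthma rows assume incompatible asthma rates (23% against an implied 17%) for what are most plausibly the same early-uninfected children

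*Protocol article*

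**What the plan says.** All of this stands in the protocol article. Under Study power, Table 2 has two rows for infant infection and asthma at 5 years, with rates in the order "Expected prevalence of outcomes (exposed vs. unexposed groups".

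- Row A: "Infant Asthma @ 5 years 1,725 1,725 35% 17% vs. 23% # 0.05 83" (power in percent). Infected children have 17% asthma and uninfected children 23%.
- Row B: "Infant Asthma @ 5 years 1,725 1,207 20% 25% vs. 15% # 0.01 93" (power in percent). The direction is reversed, with 25% in the exposed and 15% in the unexposed.

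The notes to the table estimate that "20% of children will have asthma at 5 years", that about "30% of children will have at least one documented geohelminth infection during the first 2 years of life", and that about "50% of mothers are infected with any geohelminth parasite".

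Under Hypotheses, the fourth hypothesis has two arms. Early (chronic) exposure protects against asthma, while "non-chronic exposures (i.e. later childhood exposures occurring after 2 years in the absence of maternal geohelminth infections) increase the risk of asthma". The legend to Figure 4 likewise assigns the harmful pathway to children with no early exposure who are first infected after 24 months. The table does not say who the 1,207 children in Row B are.

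**The concern.** The two rows concern one cohort, one outcome and one age, and they support the two arms of one hypothesis. If Row B is the late-infection arm, its 1,207 children are the unexposed group of Row A, split into those infected later and those never infected. The average of the split should then return Row A's 23%. It returns 17%, which is Row A's rate for the infected children.

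Asthma is a primary outcome, and a null result for early or late infection will be read against the power printed here. A reader cannot tell which baseline those powers assume, and no single description of the cohort produces both rows.

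**Working it through.** **Inputs.** Row A: N = 1,725, 35% exposed, 17% vs 23%, alpha 0.05, power 83%. Row B: N = 1,207, 20% exposed, 25% vs 15%, alpha 0.01, power 93%. Notes to Table 2: 20% asthma overall, about 30% infected by age 2, about 50% of mothers infected. The article does not state sidedness; two-sided tests are assumed.

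**Formula.** Power = Φ[(|p1 − p2| − z·s0)/s1], with s0 = √{p̄(1 − p̄)(1/n1 + 1/n2)} and s1 = √{p1(1 − p1)/n1 + p2(1 − p2)/n2}. The continuity-corrected version first subtracts ½(1/n1 + 1/n2) from |p1 − p2|. Results are given as plain / corrected.

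**1. The plan's own figures.**
- Row A, 604 vs 1,121: (0.06 − 1.960 × 0.02052)/0.01979 = 1.00, so 84.1% / 82.5%. The printed 83% reproduces.
- Row B, 241 vs 966, alpha 0.01: (0.10 − 2.576 × 0.02703)/0.03015 = 1.01, so 84.3% / 82.2%. The printed 93% does not reproduce. At alpha 0.05 the same inputs give 94.1% / 93.0%. This alpha mismatch is separate from the rate conflict, but it sets the right comparator for Row B: 82-84%, not 93%.

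**2. Who the 1,207 are.** 0.70 × 1,725 = 1,207.5, the share left after removing the 30% infected early. The reversed direction matches the late-infection arm. They cannot all be children of uninfected mothers, because 0.50 × 1,725 is only about 862. So the early-uninfected children are the most plausible reading, though an inferred one.

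**3. The rate conflict.**
- Row B's pooled rate is 0.2 × 25% + 0.8 × 15% = 17%. Row A's unexposed rate is 23%.
- The gap between 35% and 30% exposed does not explain it. Row A puts 0.23 × 1,121 ≈ 258 cases among its unexposed; Row B allows 0.17 × 1,207 ≈ 205 cases in a larger group.
- To reach 20% overall with 70% of children at 17%, the early-infected need (0.20 − 0.70 × 0.17)/0.30 = 27%.
- Row A alone averages 0.35 × 17% + 0.65 × 23% = 20.9%, close to the 20% in the notes.

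**4. Early-infection power after alignment to 20% overall (alpha 0.05).**

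| Held fixed | Exposed | Rates | Power |
|---|---|---|---|
| 6-point difference | 30% (518 vs 1,207) | 15.8% vs 21.8% | 83% / 81% |
| Early-infected at 17% | 30% (518 vs 1,207) | 17% vs 21.3% | 53% / 51% |
| Early-infected at 17% | 35% (604 vs 1,121) | 17% vs 21.6% | 63% / 61% |

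The 21.3% is (0.20 − 0.30 × 0.17)/0.70; the 21.6% is (0.20 − 0.35 × 0.17)/0.65.

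**5. Late-infection power after alignment (241 vs 966, alpha 0.01).** Row B's odds ratio is (0.25/0.75)/(0.15/0.85) = 1.89.

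| Pooled rate in the 1,207 | 10-point difference | Odds ratio 1.89 |
|---|---|---|
| 21.3% | 29.3% vs 19.3%: 78% / 75% | 90% / 88% |
| 23% | 31% vs 21%: 75% / 72% | 32.8% vs 20.5%: 91% / 90% |

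Holding the risk ratio at 25/15 with a 23% pool gives 96%.

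**The case against.** The strongest defence is that each power is conditional on its own row's inputs. Row A's 83% is correct on that basis, and the notes say the asthma effects come from cross-sectional analyses elsewhere, so different planning rates per row may be loose but are not an arithmetic error. That stands for Row A's power figure. It does not make the rates compatible.

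A reader might go further and infer that the two powers exclude each other, or that early-infection power must be far below 83%. The documents do not support this. One coherent set is 15.8% (infected by 2 years), 31.3% (first infected later) and 19.4% (never infected). The last two average 0.2 × 31.3% + 0.8 × 19.4% = 21.8%, and the whole cohort averages 0.3 × 15.8% + 0.7 × 21.8% = 20.0%. It gives 83% / 81% for early infection at alpha 0.05 and 90% / 89% for late infection at alpha 0.01. The 51-63% range arises only when 17% and 20% are both held, which shrinks the early effect from 6 points to 4.3 (30% exposed) or 4.6 (35% exposed). Likewise, measuring an aligned late-infection power against the printed 93% would blame the rate conflict for a gap that is largely the alpha mismatch.

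It is also fair that the identity of the 1,207 is inferred. Row A's unexposed number 1,121, and the hypothesis adds a condition ("later childhood exposures occurring after 2 years in the absence of maternal geohelminth infections") that Row B does not apply. But if the 1,207 were instead a representative subset, their 17% would still disagree, by less, with the 20% in the notes and the 20.9% implied by Row A.

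**Conclusion.** The rate conflict holds: 23% in one row against an implied 17% in the other, and a 17% pool meets the stated 20% overall only if early-infected children have about 27%. This rests on reading the 1,207 as the children uninfected by age 2, which the 70% share and the late-infection hypothesis support but the table does not state.

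Its effect on power is undetermined in size, and for late infection in direction, until the planning choices are fixed. Early-infection power could stay near the printed 83% or fall to about half. Late-infection power could lie below or above the 82-84% that Row B's own inputs give at alpha 0.01. The finding is that the asthma power statements rest on inputs that cannot describe one cohort. It does not show that the study is underpowered for asthma.

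**What to change.** In Table 2 and its notes:

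1. State who the 1,207 children are, and whether the absence of maternal infection is part of the late-exposure definition used for that row.
2. Replace the two rows' rates with one set of three (infected by 2 years; first infected later; never infected) whose weighted mean is about 20%.
3. Use one early-exposure prevalence, 30% or 35%, in both rows.
4. State which effect measure is held fixed (difference, odds ratio or risk ratio).
5. Recompute both powers at the printed alpha, and restate the asthma power in the text of Study power to match.

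The cost is two table rows, a line in the notes and a sentence. The sample size is fixed and data collection does not change. The restated power may be less favourable than the printed figures.

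### Table 2's last asthma row prints 93% power at α = 0.01, but its own inputs give 82–84%; 93% is what they give at α = 0.05

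*Protocol article*

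**What the plan says.** Table 2 of the Protocol article (Study power) gives one line of inputs and one power figure for each exposure–outcome pair. The last line concerns infant exposure and asthma at 5 years, with 1,725 children available. Its remaining cells are "1,207 20% 25% vs. 15% # 0.01 93", the final figure being a percentage. The column heading for the two outcome rates is "Expected prevalence of outcomes (exposed vs. unexposed groups", so 25% belongs to the exposed and 15% to the unexposed.

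The infant asthma row directly above uses a different α: "1,725 35% 17% vs. 23% # 0.05 83". The maternal asthma row above that also uses 0.05, with 86% power.

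The article states no formula, sidedness, continuity correction or software. The text introducing the table expects power of at least 80% at α = 0.01 for most outcomes, a level "that will allow for the loss of power expected by controlling for confounding".

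**The concern.** A power figure should follow from the inputs printed beside it. Here 93% does not follow at α = 0.01, while it does follow at the 0.05 level used in the two asthma rows above.

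The row matters because of what it appears to support. Its effect runs in the harmful direction, with more asthma among the exposed. Its 1,207 children are 70% of the 1,725 available (0.70 × 1,725 = 1,207.5), which matches removing the roughly 30% that the table note expects to be infected in the first 2 years. It therefore looks like the power case for the second half of hypothesis 4 (Hypotheses), that first exposure after age 2 raises asthma risk. No other row has that direction of effect. This reading is an inference, because the row is labelled only as infant exposure.

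If 93% is wrong, the reader is told that the chance of missing the effect is 7% when it is more than twice that. The room left for confounder adjustment is overstated as well.

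**Working it through.** **Inputs, all from the last row of Table 2**

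- N = 1,207. The column is "Analysis sample size", so no further dropout applies.
- Exposed share 20%: n₁ = 0.20 × 1,207 = 241.4 and n₂ = 965.6.
- p₁ = 0.25, p₂ = 0.15, difference d = 0.10.
- α = 0.01, printed power 93%.
- Sidedness is not stated. The Hib row, "1,000 50% 65% vs. 75% 0.01 80", settles it: two-sided formulas give 79–81% there and one-sided formulas 86–87%, against the printed 80%. Two-sided is used below.

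**Formula (two proportions, pooled variance under the null)**

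Power = Φ[(d − z·SE₀)/SE₁], where

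- p̄ = 0.20 × 0.25 + 0.80 × 0.15 = 0.17
- SE₀ = √[0.17 × 0.83 × (1/241.4 + 1/965.6)] = 0.02703
- SE₁ = √[0.25 × 0.75/241.4 + 0.15 × 0.85/965.6] = 0.03015
- continuity correction: subtract ½(1/241.4 + 1/965.6) = 0.00259 from d

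**Attempt to reproduce 93% at the printed α = 0.01 (z = 2.576)**

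- Pooled: (0.10 − 2.576 × 0.02703)/0.03015 = 1.008, power 84.3%.
- Continuity-corrected: (0.09741 − 2.576 × 0.02703)/0.03015 = 0.922, power 82.2%.

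**The same row at α = 0.05 (z = 1.960)**

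- Pooled: (0.10 − 1.960 × 0.02703)/0.03015 = 1.560, power 94.1%.
- Continuity-corrected: (0.09741 − 1.960 × 0.02703)/0.03015 = 1.474, power 93.0%.

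**Other methods at two-sided α = 0.01**

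| Method | Power |
|---|---|
| Unpooled variance | 77.1% |
| Simple average p̄ | 80.5% |
| Arcsine | 82.2% |
| Log-odds Wald | 86.1% |
| Exact enumeration, chi-square | 84.5% |
| Exact enumeration, Yates | 82.3% |
| Exact enumeration, likelihood ratio | 82.7% |
| Exact enumeration, Wald | 84.2% |

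A one-sided α of 0.01 gives 83.9–90.9% across the approximate formulas. No method reaches 93%.

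**Calibration on other rows, two-sided at each row's own α**

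| Row | Printed | Pooled | Continuity-corrected |
|---|---|---|---|
| Hib, 7 months | 80% | 81.1% | 79.1% |
| HBV, 2 years | 80% | 78.6% | 76.8% |
| HBV, 5 years | 95% | 95.7% | 95.1% |
| Eczema, 3 years | 99% | 98.3% | 98.1% |
| Maternal asthma, 5 years | 86% | 87.7% | 86.4% |
| Infant asthma, 35% exposed | 83% | 84.1% | 82.5% |
| **Infant asthma, 20% exposed** | **93%** | **84.3%** | **82.2%** |

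The seven rows not listed come out above 99% under both formulas, in line with print. Under the pooled formula, 13 of the 14 rows lie within about 2 points of print. Only the last row fails.

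**What would give about 93% with α = 0.01 kept**

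- About 30% exposed (362 of 1,207): 92.8% pooled, 91.7% corrected.
- The 20% taken as a share of all 1,725 (345 exposed, or 28.6% of 1,207): 92.1% pooled, 90.9% corrected, 93.1% log-odds.
- 20% exposed and a larger sample: about 1,575 children, or 1,635 with continuity correction.

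Each of these departs from the printed row.

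**The case against.** The mismatch itself is hard to dispute. The case on the other side concerns cause and weight.

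- **Cause.** A wrong α label is not the only candidate. If 20% means a share of the 1,725 available, 345 of the 1,207 are exposed, and the log-odds formula gives 93.1% at α = 0.01. That is the scale of the planned logistic regression, and the same formula gives 83.0% for the infant asthma row above, as printed. Small changes in the outcome rates also suffice: 26.5% vs 15% gives about 93% pooled, and 25% vs 13.5% gives 93.3% corrected. Nor does the continuity-corrected formula fit every row; it gives 76.8% for HBV at 2 years, printed as 80%. **This stands in part.** The cause cannot be proved. But every alternative contradicts a printed cell, so none makes the row correct as it is.
- **Weight.** The cohort is fixed at 2,403 and recruitment is over, so this cell sets no sample size and no analysis. At 82–84% the row still meets the article's own mark of 80%. The inputs are rough: moving the exposed rate from 25% to 26% lifts pooled power to about 91%. **This stands.** It limits the consequence but does not turn 84% into 93%. Uncertain inputs are a reason to show a range, not to print a figure that they do not give.
- **Link to hypothesis 4.** The document does not say that this row serves it. **This stands**, and the link is treated here as an inference.

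**Conclusion.** The concern holds. At the printed inputs and two-sided α = 0.01, power is 82–84% (77–86% across all two-sided methods tried), not 93%. The overstatement is 9 to 11 points (93 − 84.3 = 8.7; 93 − 82.2 = 10.8). The type II error is 16–18% rather than 7%, more than double.

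The margin above 80% falls from 13 points to about 2–4, before any loss from confounder adjustment. That loss is not built into the table, and the article gives no figure for it.

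A computation at α = 0.05 is the simplest explanation, since the continuity-corrected formula then gives 93.0% and also matches the two asthma rows labelled 0.05. It remains a probable cause, not a demonstrated one.

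The result rests on a two-sided test, supported by the Hib row, and on 20% being the exposed share of the 1,207 analysed, as the table's layout implies. The stated figure is wrong and needs correcting. The practical effect is modest, because the design is fixed and unadjusted power stays above 80%.

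**What to change.** Check the original calculation and correct whichever cell in the row is wrong:

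- If α = 0.01 and 20% exposed are intended, print power as 82–84% (84% pooled, 82% continuity-corrected).
- If the calculation was made at α = 0.05 and that is the level to be used, relabel α as 0.05 and keep 93%.
- If the exposed share of the 1,207 is nearer 30%, correct the exposure cell and recompute.

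Name the formula and the sidedness in the table note so that every row can be reproduced. If the analysis set for the later-exposure part of hypothesis 4 is revised, recompute the row on that set.

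The cost is one table cell and a line of note, plus a less favourable stated power if α = 0.01 is kept. Nothing changes in recruitment, data collection or analysis.

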### Measurement and definitions of study outcomes

#### Primary study outcomes

1. *Vaccine immune responses: *vaccine immunity will be measured by the presence of protective antibody levels measured as follows-1) IgG to tetanus toxoid as described previously [46]. Immune protection will be defined > 0.15 IU/ml; 2) titer of neutralizing antibodies to OPV type 3 using the microneutralization assay at the Health Protection Agency (HPA), London, UK. Protection will be defined as OPV type 3 virus neutralization at 100TCID50 at serum dilution ≥ 1:8 dilution; 3) IgA to rotavirus (HPA); protection indicated by titers ≥ 20 U/mL; 4) IgG to polyribosylribitol phosphate of *Haemophilus influenzae *type B (Binding site, Birmingham, UK); protection > 0.15 mg/mL; 5) anti-HBS IgG antibodies (Architect, Abbott Diagnostics, Sligo, Ireland), protection > 10 IU/mL IgG. Plasma samples collected at 24 months and 5 years will be used to measure short-term (24 months) and long-term (5 years) antibody-mediated protective immunity. Vaccine responses to Hib and rotavirus will be measured only at 7 months to distinguish vaccine-mediated responses from those acquired from natural exposures to these infections.

2. *Atopy: *defined by the presence of allergen skin test reactivity at 5 years to any of the following aeroallergens: *Dermatophagoides pteronyssinus/farinae *mix, American cockroach (*Periplaneta americana*), fungi mix, dog, cat, and mixed grass pollen. A positive test is defined by the presence of a skin wheal ≥ 3 mm greater than saline control. All skin testing will be conducted by trained physicians and will be supervised by a highly experienced clinical investigator ([name]).

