### Study limitations

We expect losses to follow-up to be up to 10% in the first year (i.e. 2,163/2,403 followed up) and 5% annually to age 3 and a further 5% between ages 3 and 5. Estimates for the number of children followed-up are: 2 years-2,055, 3 years-1,952, and 5 years-1,854. Losses are due to the mobility of the study population.

Potential sources of biases are selection bias caused by losses to follow up and information bias caused by systematic misclassification of outcomes. The following methods are being used to minimize these biases: *Achieving high rates of follow-up *- a) we have a well-trained study team employed full-time for the cohort; b) we conduct regular home visits to maintain contact with study mothers; c) the universal use of mobile phones allows us to maintain regular contact with study mothers; d) the mother of each child is given a cohort identification card with a phone number to make appointments at the ECUAVIDA outpatient Clinic; e) changes of address are followed up actively with home visits to repeat environmental sampling. *Information bias *- a) repeated measurements of outcomes (for asthma, eczema, and allergen skin test reactivity) should reduce misclassification and recall bias; b) clear definitions for primary outcomes and exposures; c) evaluation of outcomes is being performed blind to exposure status. Detailed information on potential confounding factors is being collected.

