### Analysis plan

Statistical analysis will be guided by the conceptual frameworks presented for each of the study outcomes (Figures 2, 3, 4 and 5). The analysis of the primary study outcomes will use multiple logistic regression to estimate the Odds Ratios for exposure-outcome associations with adjustment for appropriate confounding factors. For example, *a priori *confounders for the association between maternal geohelminth infections and eczema by 3 years of age are gender, maternal educational level, household crowding, and infant geohelminth infections. The primary analyses will evaluate the effects of maternal geohelminth infections or infant geohelminth infections on: 1) protective immunity to common childhood vaccines: 2) the presence of allergen skin test reactivity at 5 years of age; 3) the development of eczema by 3 years of age; and 4) the development of asthma at 5 and 8 years of age. Immunological variables will be defined as binary variables with a cut-off defined by the limit of detection of the assays (i.e. IL-10) or median level (i.e. IL-8) or as log_e_-transformed continuous variables. Because immunological variables are considered as intermediate in the causal pathways between exposures and outcomes, these variables will be evaluated in hierarchical analyses [60].

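### Table 2 conflicts with the rest of the article on skin-test age, infant exposure, cohort size and alpha, and one asthma power (93%) does not follow from its own row

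*Protocol article*

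**What the plan says.** All references are to the protocol article.

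- **Skin-test age.** Primary study outcomes sets atopy as "defined by the presence of allergen skin test reactivity at 5 years to any of the following aeroallergens", and the Analysis plan lists "the presence of allergen skin test reactivity at 5 years of age". Table 2 powers it at 3 years: "Maternal SPT @ 3 years 1,840 1,840 50% 15% vs. 25% 0.01 99" and "Infant SPT @ 3 years 1,840 1,840 35% 15% vs. 25% 0.01 > 99" (percent).
- **Infant exposure.** Five infant rows of Table 2 use 35%. The footnote, citing cohort data, says that about "30% of children will have at least one documented geohelminth infection during the first 2 years of life".
- **Cohort size.** Study limitations: "Estimates for the number of children followed-up are: 2 years-2,055, 3 years-1,952, and 5 years-1,854". Table 2 lists 1,955, 1,840 and 1,725 as available at the same ages.
- **Alpha.** Eleven rows use 0.01. Hepatitis B at 2 years and the two asthma rows with 17% vs 23% use 0.05. Hepatitis B at 5 years uses 0.01. The Study power text cites power of at least 80% at alpha 0.01 for most outcomes and adds that this "will allow for the loss of power expected by controlling for confounding".
- **Last asthma row.** Labelled infant exposure: n = 1,207, 20% exposed, 25% vs 15%, alpha 0.01, power 93%.

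**The concern.** Table 2 is the only quantitative support for a fixed sample of 2,403. As printed, no row powers the skin-test outcome that the article calls primary. A reader also cannot tell which infant prevalence, cohort size or significance level applies to the primary analyses.

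The text gives two general assurances: at least 80% power at alpha 0.01 for most outcomes, and room for adjustment. The primary analysis is confounder-adjusted logistic regression, so a row that reaches 80% only before adjustment does not support the second assurance.

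A power overstated by about 10 points in the last asthma row would mislead on the risk-increasing comparison, the only row in which exposure raises prevalence.

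**Working it through.** **Method.** Sidedness and formula are not stated. A two-sided comparison of two proportions with pooled variance under the null fits the table. With exposed share e, n1 = eN, n2 = (1−e)N and pooled proportion p:

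- SE0 = √[p(1−p)(1/n1+1/n2)]
- SE1 = √[p1(1−p1)/n1 + p2(1−p2)/n2]
- power = Φ[(|p1−p2| − z·SE0)/SE1], with z = 1.960 at alpha 0.05 and 2.576 at alpha 0.01

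The continuity-corrected version (cc) subtracts ½(1/n1+1/n2) from |p1−p2|.

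**Step 1: each row on its own inputs (%).**

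| Row | Stated | Computed | cc |
|---|---|---|---|
| Hib, 7 months | 80 | 81.1 | 79.1 |
| Rotavirus, 7 months | >99 | >99.9 | >99.9 |
| Tetanus, 2 years | >99 | 99.7 | 99.6 |
| Hepatitis B, 2 years | 80 | 78.7 | 76.8 |
| Polio type 3, 2 years | >99 | 99.5 | 99.2 |
| Tetanus, 5 years | 99 | >99.9 | >99.9 |
| Hepatitis B, 5 years | 95 | 95.7 | 95.2 |
| Polio type 3, 5 years | >99 | >99.9 | >99.9 |
| Skin test, maternal | 99 | 99.8 | 99.7 |
| Skin test, infant | >99 | 99.5 | 99.4 |
| Eczema | 99 | 98.3 | 98.1 |
| Asthma 17 vs 23, maternal | 86 | 87.7 | 86.4 |
| Asthma 17 vs 23, infant | 83 | 84.1 | 82.5 |
| Asthma 25 vs 15, last row | **93** | **84.3** | **82.2** |

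Thirteen rows agree to within about 3 points. The largest gap among them is hepatitis B at 2 years.

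**Step 2: the last asthma row.** n1 = 0.20 × 1,207 = 241.4; n2 = 965.6; p = 0.17; SE0 = 0.02703; SE1 = 0.03015. At alpha 0.01: (0.10 − 2.576 × 0.02703)/0.03015 = 1.008, so power is 84.3%. At alpha 0.05: (0.10 − 1.960 × 0.02703)/0.03015 = 1.560, so power is 94.1% (cc 93.0%). Unpooled variance at 0.01 gives 77.1%, and a one-sided 0.01 test gives 89.1%. With the other entries as printed, 93–94% appears only at two-sided alpha 0.05.

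**Step 3: hepatitis B at 2 years.** n1 = n2 = 875; p = 0.825; SE0 = 0.01817; SE1 = 0.01813. (0.05 − 1.960 × 0.01817)/0.01813 = 0.794, so power is 78.7% (cc 76.8%). With all 1,955 available children it is 82.9% (cc 81.4%).

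**Step 4: the three alpha 0.05 rows, recomputed at 0.01.** Hepatitis B at 2 years 57.0% (cc 54.5%); maternal asthma 70.6% (cc 68.5%); infant asthma 64.1% (cc 61.6%).

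**Step 5: where the sample sizes come from.** Study limitations: 2,403 × 0.90 = 2,163, then × 0.95 three times gives 2,055, 1,952 and 1,854. Table 2: 2,300 × 0.85 = 1,955; × 0.80 = 1,840; × 0.75 = 1,725. Table 2 is the smaller set at every age.

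**Step 6: effect of reconciling the inputs (%).**

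| Comparison | Stated | Corrected inputs | Power (cc) |
|---|---|---|---|
| Infant skin test, 5 years | >99 | 30%, n = 1,725 | 98.6 (98.3) |
| Infant skin test, 5 years | >99 | 30%, n = 1,854 | 99.1 (99.0) |
| Maternal skin test, 5 years | 99 | 50%, n = 1,725 | 99.6 (99.5) |
| Infant hepatitis B, 5 years | 95 | 30%, n = 1,500 | 94.1 (93.3) |
| Infant asthma, alpha 0.05 | 83 | 30%, n = 1,725 | 80.9 (79.0) |
| Infant asthma, alpha 0.05 | 83 | 30%, n = 1,854 | 83.7 (82.0) |

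**The case against.** The best defence is that the table mostly works. Thirteen of 14 powers follow from their printed inputs. The 30% vs 35% and cohort-size discrepancies pull in opposite directions and nearly cancel. Each row prints its alpha, and the text claims 80% at 0.01 only for most outcomes. Hepatitis B at 78.7% without continuity correction could be rounding. The vaccine rows use random subsamples, so more samples could be assayed. All of this stands, and it limits the size of the point.

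It also rules out several stronger readings that a reader might infer:

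- *That several stated powers are wrong.* Only the last asthma row is clearly wrong on its own inputs.
- *That the stated infant-asthma power is not delivered.* The drop to 79–81% comes from combining 30% exposure with the smaller n of 1,725. With 1,854 it is 82–84%.
- *That the sample sizes inflate power.* Table 2's figures are conservative, and children with usable samples may be fewer than children followed up.
- *That alpha was relaxed to rescue weak rows.* The three 0.05 rows are the ones clearly below 80% at 0.01, but the article gives no reason for the choice, so motive is conjecture.
- *That the mixed alphas imply a particular overall false-positive rate.* The article says "Primary outcome variables will be treated as statistically independent" and sets no family-wise target. Any such rate would need all null hypotheses true and all rows independent.

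The defence does not remove the missing 5-year skin-test row, the 93% figure, or the claim of a reserve in rows at about 80%.

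**Conclusion.** The point holds as a set of internal inconsistencies plus one clear numerical error.

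- The last asthma row overstates power by about 9 to 11 points: 93% stated, 82–84% at its printed alpha.
- Hepatitis B at 2 years is 77–79% against 80%, and Hib is 79–81%. Neither has a reserve for adjustment at its planned sample size.
- The claim of at least 80% at alpha 0.01 does not extend to hepatitis B at 2 years (about 57%) or to the two 17% vs 23% asthma rows (about 71% and 64%). These powers are valid at the 0.05 they print, but the text does not mention the exception.
- Skin-test age, infant exposure and cohort size need reconciling for consistency. Their effect on power is small.

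The figures assume two-sided tests and the normal approximation, with the continuity correction giving the lower end of each range. They use the article's own expected prevalences. The design is not undermined.

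**What to change.** 1. Recompute Table 2 with the skin test at 5 years, about 30% infant exposure in the five early-infection rows, and sample sizes reconciled with Study limitations (or a note on why fewer are available).
2. Keep the last asthma row's separate 20% group. Substituting 30% there gives 92.8% at alpha 0.01 and would hide the error. Correct its power to about 82–84% at alpha 0.01, or correct its alpha if 0.05 was meant.
3. Restate hepatitis B at 2 years as about 77–79%, or plan to assay all 1,955 available samples (81–83% at alpha 0.05).
4. State in the text that hepatitis B at 2 years and the 17% vs 23% asthma comparisons are powered at alpha 0.05 only.
5. Remove the claim of a reserve for confounding for rows near 80%.

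The cost is a revised table and a few sentences, with some figures less favourable. Assaying all available samples for hepatitis B would add 1,955 − 1,750 = 205 assays.
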